### Quality control system for the research

2.5

To maintain scientific rigor, patient safety, and compliance, this study includes several quality control measures, as detailed below:

#### Patient compliance management

2.5.1

Patient compliance with SBP and exercise plans will be monitored via a follow-up platform and WeChat group, involving clinicians, rehabilitation physicians, patients, and families. Patients are required to upload daily exercise data. Nurses will communicate in-person with those who miss one or more times of follow-ups. Compliance is defined as logging in more than 3 days a week. The staffing arrangements for routine monitoring and follow-up are shown in Table 8.

**Table 8 tab8:** Regular follow-up and monitoring team.

Personnel category	Qualification requirements	Core responsibilities
Rehabilitation physician	Possess cardiovascular rehabilitation qualification	a. Develop personalized plans: determine exercise intensity (low/medium/high), exercise type (Baduanjin, brisk walking, etc.) and progress based on CPET; b. Provide technical guidance: responsible for on-site technical demonstration of Phase I rehabilitation and solving medical problems during exercise; c. Supervise safety: evaluate patients’ IMR based on rechecked CPET results every quarter to adjust exercise plans
Full-time research nurse	Hold cardiovascular specialist nurse certificate	a. Phase I rehabilitation: under the guidance of rehabilitation physicians, assist in on-site supervision of daily rehabilitation training; b. Remote follow-up: responsible for regular follow-up of patients 1–12 months after revascularization, including weekly telephone follow-up, receiving patients’ exercise data, and feeding back abnormal data to rehabilitation physicians; c. Compliance management: conduct targeted communication via phone calls, WeChat groups, etc. with patients who fail to complete exercise as required or miss data submission, analyze the reasons and provide solutions; d. Medication reminder: send medication reminders to patients through the research-WeChat groups at fixed times (7:00 a.m., 12:00 p.m., 7:00 p.m.) daily, and record whether patients take the medicine on time. e. Adherence intervention: for patients with poor medication adherence (such as missing doses frequently), communicate with them to find out the reasons (like forgetting, worrying about side effects) and provide targeted solutions.
Rehabilitation therapist	Possess practical qualification in exercise rehabilitation	a. Phase II rehabilitation: correct exercise postures, guide flexibility training and 4–7-8 breathing technique; b. Phase III rehabilitation support: record standardized exercise teaching videos and upload them to WeChat groups
Cardiovascular SPECIALIST	–	a. Safety control: complete exercise risk stratification for participants during enrollment and exclude high-risk patients; b. Emergency medical support: responsible for evaluation and handling of adverse events during follow-up; c. Medication education: provide patients with detailed medication education before they start taking SBP, including the dosage, frequency, time of administration, possible side effects, and the importance of adherence
Patient’s family	Voluntarily participate and receive training	a. Assist in supervision: remind patients to complete daily training as scheduled; Remind patients to take SBP on time every day according to the prescribed dosage and frequency; b. Emergency training: receive special training on CPR and be able to initially handle emergencies occurring during home-based exercise; c. Feedback communication: keep in touch with the research team (full-time research nurses) and feedback patients’ medication status (whether they take the medicine as required, any abnormal reactions) in a timely manner

#### Safety assurance

2.5.2

##### Exercise safety

2.5.2.1

Rehabilitation physicians will offer online and offline exercise guidance. Before starting, patients will receive a thorough assessment, including medical history, symptoms, physical exams, and tests. Physicians will advise on exercise precautions and joint protection for safety.

##### Drug safety

2.5.2.2

The long-term safety of SBP will be assessed through the monitoring of hepatic and renal function, metabolic processes, and nutrition-related indicators.

##### Comprehensive safety

2.5.2.3

Before the study, patients will undergo a thorough assessment of cardiovascular, muscular, psychological, and vascular functions to identify risks. Personalized rehabilitation plans will be created from these evaluations, with strict control over the intensity and progress for high-risk patients. Facilities are equipped with first-aid equipment and medications, and medical staff are skilled in first-aid procedures.

#### Standardized data collection

2.5.3

Data collectors will undergo professional training on standard procedures. Patient information will be recorded using a standardized spreadsheet for consistency. Blood test data collection will adhere to aseptic principles to avoid errors. An electronic medical record system will enable real-time data input and storage, aiding management and queries. Regular reviews will ensure timely corrections and updates.

#### Exercise intensity adjustment

2.5.4

Cardiopulmonary exercise tests (CPET) will be administered on a quarterly basis to assess the microcirculation resistance index (IMR). Should the IMR surpass a threshold of 25, the exercise intensity will be adjusted accordingly to accommodate the specific requirements of each patient.

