### Intervention measures

2.3

As an interventional trial, blinding of participants, treating physicians, and researchers directly involved in intervention implementation was not feasible due to the specific nature of the interventions (including oral SBP and exercise rehabilitation training), whose distinct characteristics would render blinding impractical. Importantly, outcome assessors responsible for data collection and statisticians conducting post-data-collection analyses remained blinded to group allocation throughout the study.

If a participant learns their group assignment during rehabilitation exercises, they will be assessed. If this knowledge could influence their behavior, they may be excluded from the study. Additionally, other participants will be monitored for information leaks. If others are affected, measures like re-evaluating data validity or exclusion from the study will be taken.

Tables 1–6 show the details content of the pre-exercise assessment, the three-phase exercise prescription, the exercise intensity grading, the type of exercise, the remote monitoring, and the outpatient period training program, respectively. The principles of full-cycle rehabilitation are shown in Figure 2. The schedule in this study is shown in Figure 3.

**Table 1 tab1:** Pre-exercise assessment.

Component	Detailed design
Cardiopulmonary function	CPET to measure VO_2_ peak and anaerobic threshold (AT)
Exercise risk stratification	AACVPR risk stratification criteria (incorporating LVEF, arrhythmia history)
Muscle function evaluation	30-s chair stand test, grip strength measurement
Psychological assessment	Hospital anxiety and depression scale (HADS)
Vascular evaluation	Coronary flow reserve (CFR), index of microcirculatory resistance (IMR, optional)

CPET, cardiopulmonary exercise test; AACVPR, American Association of Cardiovascular and Pulmonary Rehabilitation, LVEF, left ventricular ejection fraction.

**Table 2 tab2:** Three-phase exercise prescription.

Phase	Timeframe	Primary goals	Monitoring	Termination Criteria
Phase I	(Inpatient) 2–7 days post-PCI	Prevent deconditioning	Daily assessment	Chest pain > CCS Class II, SpO2 < 90%
Phase II	(Outpatient) 1–6 months post-discharge	Improve aerobic capacity	Weekly onsite + remote	ST depression ≥2 mm, SBP drop >10 mmHg
Phase III	(Home-based) 7–12 months	Long-term maintenance	Monthly follow-up	New-onset VT/AF

CCS, Canadian Cardiovascular Society, VT’AF, ventricular tachycardia/atrial fibrillation.

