**Table 3 tab3:** Based on CPET exercise intensity grading.

Intensity grading based on CPET	Target parameters	Applicable phases	Patient characteristics
Low intensity	40–50% of HR_peak_, RPE 11–12	Phase I/high-risk patients	LVEF < 45%, NYHA functional class II
Moderate intensity	60–70% of HR_peak_, RPE 13–14	Core of Phase II	No residual ischemia, ≥5 METs
High intensity	80–85% of HR_peak_, RPE 15–16	Optimization of Phase III	Young, low-risk, and well-adapted

RPE, rating of perceived exertion, LVEF, left ventricular ejection fraction NYHA, New York Heart Association; METs, metabolic equivalents.

**Table 4 tab4:** Type of exercise training.

Exercise modality	Details
Outdoor Aerobic training	Method: brisk walking Frequency: 3–5 times a week; duration: 30–45 min per session. Progression: increase the duration or intensity by 5% every month, or increase the walking distance and speed gradually according to your own situation.
Indoor Aerobic training	Method: Baduanjin Frequency: 3–4 times a week; duration: 12–26 min per session; take a 2-min break between each set. Precautions: perform the movements standardized, coordinate breathing with the movement rhythm, and avoid overexertion.
Flexibility training	Method: static stretching (30 s per muscle group) Focus: correcting the pectoralis major and minor muscles
Breathing training	Technique: 4–7-8 breathing technique Goal: reduce the oxygen consumption of the respiratory muscles and increase blood oxygen levels

Recorded videos of aerobic, resistance, flexibility, and breathing training will be uploaded to the WeChat for participants’ reference.

**Table 5 tab5:** Remote monitoring system.

Methods	Details
Equipment for measuring physiological indicators	Electronic blood pressure monitors
Monitoring platform	Custom APP features: - HR, resting BP, etc. upload - Exercise video upload

HR, heart rate, BP, blood pressure.

**Table 6 tab6:** Sample outpatient session (Phase II).

Time	Activity
8:00–8:30	Ambulatory BP monitoring + pre-exercise assessment (Borg scale)
8:30–8:45	Chest expansion and front raise exercise with heavy weights in hand (weight depends on the individual and increases over time)
8:45–9:30	Brisk walking: walk at a moderate speed for 30–45 min. Adjust the speed appropriately during the process to maintain the exercise intensity
9:40–10:10	Baduanjin: practice Baduanjin completely. Perform the movements standardized, coordinate breathing, and do 1–2 rounds, which takes about 12–26 min

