#### Exercise rehabilitation intervention

2.3.2

Patients in the exercise rehabilitation group will undergo a comprehensive assessment before exercise, including general function assessment, exercise risk assessment, exercise tolerance assessment, and psychological assessment. Then, the exercise intensity will be set according to their individual conditions and cardiopulmonary exercise test results. They will be divided into low-intensity, medium-intensity, and high-intensity rehabilitation groups. The exercise program will include aerobic exercise, resistance exercise, and flexibility exercise. During the hospitalization period (acute phase, phase I), the responsible nurse will guide patients to perform rehabilitation exercises. After discharge, patients will receive early outpatient rehabilitation (stable phase, phase II) and maintenance-phase outpatient rehabilitation. The responsible nurse will conduct weekly telephone follow-ups to monitor and guide patients’ exercise implementation.

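### The quarterly IMR >25 trigger for adjusting exercise intensity cannot be applied as written: it takes IMR from CPET, while Table 1 lists IMR as a separate, optional vascular test

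*Protocol article*

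**What the plan says.** Two places in the protocol article tie a quarterly exercise adjustment to IMR obtained from CPET.

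- Section 2.5.4 (Exercise intensity adjustment): "Cardiopulmonary exercise tests (CPET) will be administered on a quarterly basis to assess the microcirculation resistance index (IMR"). The rule follows: "Should the IMR surpass a threshold of 25, the exercise intensity will be adjusted accordingly".
- Table 8 (section 2.5.1), item (c) for the rehabilitation physician, under the safety duty: the physician evaluates "IMR based on rechecked CPET results every quarter to adjust exercise plans".

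Other places describe CPET and IMR differently.

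- Table 1 (section 2.3), cardiopulmonary row: "CPET to measure VO_2_ peak and anaerobic threshold (AT").
- Table 1, vascular row: CFR and "index of microcirculatory resistance (IMR, optional").
- Table 3, the CPET-based grading, sets targets as a percentage of peak heart rate with perceived exertion. Its patient descriptors include LVEF below 45% and NYHA class II for the low tier and "No residual ischemia, ≥5 METs" for the moderate tier. IMR does not appear.
- The Discussion mentions CFR and IMR in connection with CMR imaging.
- Table 7 assesses coronary microcirculation by myocardial contrast echocardiography and perfusion imaging, immediately and 1 year after revascularization.

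**The concern.** A rule with a numeric cut-off needs a measured value to compare with it. Here the value is IMR, the cut-off is 25, and the test named as its source is CPET. Elsewhere the article treats CPET and IMR as separate assessments. Staff who carry out the quarterly CPET as Table 1 describes it would hold VO2 peak and anaerobic threshold, but no IMR.

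Exercise intensity is part of the randomised intervention, and Table 8 places this check under safety supervision. If the trigger cannot be evaluated, staff must ignore it or improvise, and improvised practice may differ between patients. From the quarterly CPET records alone, nobody could later confirm that the threshold was applied.

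**Working it through.** This is a check of consistency. The cut-off of 25 is stated, not derived, so there is no plan figure to reproduce. The relevant statements are set side by side.

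| Place | What it says about CPET | What it says about IMR |
|---|---|---|
| 2.5.4 | Repeated every quarter | Assessed by CPET; above 25 triggers adjustment |
| Table 8(c) | Rechecked every quarter | Evaluated from the CPET results |
| Table 1 | VO2 peak, anaerobic threshold | Separate vascular row, optional, before exercise starts |
| Table 3 | Basis of intensity grading; peak heart rate and METs appear | Not mentioned |
| Discussion | Used to grade intensity | Linked to CMR imaging |
| Table 7 | Not mentioned | Not mentioned |

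1. **Is the CPET-to-IMR link a single slip?** No. It stands in 2.5.4 and again in Table 8(c).

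2. **Does any other text support the link?** No. Outside those two places, the quantities associated with CPET are VO2 peak, anaerobic threshold, peak heart rate and METs: four quantities, none of which is IMR. Where IMR is mentioned elsewhere (Table 1 and the Discussion), it is kept apart from CPET.

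3. **Is there a conversion from CPET results to IMR?** None is given in the text shown.

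4. **Is there another source of a quarterly IMR value?** None is shown. Table 1 makes IMR optional even before exercise starts. Table 7 uses other methods, at two time points only.

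5. **What still guides intensity without this trigger?** Section 2.3.2 says "the exercise intensity will be set according to their individual conditions and cardiopulmonary exercise test results". Table 8(a) has the physician "determine exercise intensity (low/medium/high), exercise type (Baduanjin, brisk walking, etc.) and progress based on CPET". Table 3 gives tiers by phase, and Table 2 gives stopping criteria.

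6. **How many patients are concerned?** An exercise prescription exists only in the exercise and combined arms. At 1:1:1:1 that is 2/4 = 50% of those randomised. The article gives no total sample size, so no absolute number follows.

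7. **Does the trigger enter the statistical design?** No. The sample size formula, alpha, power and the primary outcome (contrast echocardiography and perfusion imaging) do not use IMR.

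**The case against.** The best defence has four parts.

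*Table 1 is not exhaustive.* It does not say that CPET measures only VO2 peak and anaerobic threshold, and Table 3 adds further quantities. An optional IMR before exercise is also compatible with a required one later. This is fair as far as it goes: a reader might infer that the article says CPET cannot give IMR, and it does not say that. But a cut-off of 25 needs a number, no text shown says how CPET produces it, and Table 1 and the Discussion both place IMR elsewhere.

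*The article condenses a fuller protocol, and Figure 3, the schedule, is not shown.* A separate IMR measurement may be listed there. That would excuse an omission. It would not remove the conflict, because 2.5.4 and Table 8(c) would still name CPET as the source.

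*Table 8(c) could mean that repeat CPET prompts a separate IMR evaluation.* That reading is possible for Table 8(c) alone. It fits 2.5.4 poorly, where CPET is the test done to assess IMR.

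*Little is lost in practice.* Intensity is guided by other provisions, and 2.5.4 gives neither direction nor size of adjustment even when IMR is known. Risk stratification and adverse-event handling (Table 8) and control of high-risk patients (section 2.5.2.3) also remain. This stands, and it limits the point to one trigger.

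**Conclusion.** The point holds for this one trigger. As written, it cannot be applied in the exercise and combined arms, because the named test is not described as giving the value that the rule needs. It is a rule stated wrongly in two places, not a detail left to a longer document.

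Three larger conclusions might be drawn, and the document supports none of them:

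- That the exercise prescription as a whole fails. It does not: Tables 2 and 3, Table 8(a) and section 2.3.2 still govern intensity.
- That patients are shown to be at risk. The number of quarterly reviews affected would be a count of visits, not of harm, and would need an assumed sample size.
- That the primary result is compromised. IMR plays no part in the sample size, alpha or primary outcome.

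The size is therefore one intervention rule in 2 of 4 arms (50% of patients), with no numerical effect on the design. The conclusion assumes that Figure 3 and any fuller protocol contain no method for deriving IMR from CPET. It should be corrected because the rule is filed as a safety task and the correction is cheap.

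**What to change.** **Main change.** In section 2.5.4, replace the CPET-derived IMR trigger with an adjustment based on what the quarterly CPET yields. Suggested wording: *CPET will be repeated every quarter in the exercise and combined groups. Target heart rate will be recalculated from the new peak heart rate. Intensity will be raised, held or lowered according to the change in VO2 peak and anaerobic threshold, using pre-specified cut-offs. A patient with LVEF below 45% or NYHA class II stays in the low tier whatever the METs achieved.*

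The cut-offs and the direction of each adjustment are for the sponsor's rehabilitation and cardiology team to set. The last sentence keeps Table 3's low-tier markers, so that METs alone do not move such a patient up. In Table 8(c), refer to the rechecked CPET results themselves and remove IMR as something evaluated from them. The optional IMR in Table 1 can stay.

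**Cost.** Two wording changes and a clinical decision on cut-offs. No extra tests are needed, since quarterly CPET is already planned. The downside is the loss of a microvascular input to the exercise prescription, in a trial about microvascular function.

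**Alternative.** If the sponsor wants to keep IMR above 25 as a trigger, the protocol must name an actual IMR method, schedule it, and state how intensity changes when the threshold is passed. That needs tests beyond the quarterly CPET.

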#### Emergency response plan

2.5.5

Patients will receive an emergency kit with nitroglycerin spray for angina pectoris relief. Family members will be trained in cardiopulmonary resuscitation (CPR) to improve their emergency response skills.

### Data monitoring

2.6

The Data Monitoring Committee (DMC) is composed of supervisors and statistical professionals, and all raw data will be submitted to the management department. As a low-risk intervention study, participants are not anticipated to be exposed to any harmful risks.

### Harm

2.7

In low-risk studies, the chance of serious adverse events (SAEs) is very low. Adverse events (AEs) may involve patient complaints. Specialized hospital organizations can handle these issues anytime and anywhere. If a subject experiences a serious adverse event due to the intervention during the trial, free treatment or financial compensation will be provided based on medical assessment.

### Auditing

2.8

The Ethics Committee convenes regularly. The Project Management Group performs monthly checks and reporting. The Trial Steering Committee holds monthly meetings to oversee trial progress. The DMC conducts data reviews every 3–6 months.

### Statistical analysis

2.9

In this study, there is currently insufficient reference data based on the primary outcome to support sample size calculations; therefore, pilot studies are being conducted to obtain the key parameters required for the formula:

$$n=\varphi^{2}(\sum S_{i}^{2}/g)/[\sum {\left({\bar{X}}_{i}-\bar{X}\right)}^{2}/(g-1)]$$

(where the formula parameter *g* = 4, representing a total of 4 groups in the study) to estimate the required sample size scientifically and accurately, with the significance level set as two-tailed *α* = 0.05, the statistical power set as 1-*β* = 90% (*β* = 0.1), and after calculating the theoretical sample size for each group using the formula upon completion of the pilot studies, a 20% dropout rate will be considered to adjust the theoretical sample size to obtain the final sample size for each group, with the total sample size of the study being the final sample size of each group multiplied by 4.

Statistical analyses will be conducted using appropriate methodologies based on the data characteristics. Continuous variables will be reported as means ± standard deviations, while categorical variables will be presented as frequencies and percentages. Group differences will be assessed using t-tests, analysis of variance (ANOVA), or chi-square tests, as appropriate. A *p*-value of less than 0.05 will be considered indicative of statistical significance. All statistical analyses will be conducted using software such as SPSSAU.

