### Study design

2.1

This study is a prospective, single-center, randomized controlled clinical trial. Patients with CTO who underwent PCI in the cardiology department of our hospital. Using a computer-generated block randomization sequence (block size = 4), participants were allocated in a 1:1:1:1 ratio to one of four parallel groups: the SBP group, the exercise rehabilitation group, the combined SBP and exercise rehabilitation group, and the control group. Allocation concealment was ensured by a central randomisation module embedded in the Hospital Information System (HIS); the treatment assignment was automatically released only after the participant had been registered and baseline data entry was completed. Figure 1 shows the details of the study process. This study will strictly adhere to the Standard Protocol Items: Recommendations for Interventional Trials (SPIRIT) reporting standard (20).

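### Section 2.9 takes the effect in the sample-size formula from pilot group means, so typical n is too small and expected power is below the stated 90%

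*Protocol article*

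**What the plan says.** Section 2.9 (Statistical analysis) starts from the position that "there is currently insufficient reference data based on the primary outcome to support sample size calculations", and continues that "pilot studies are being conducted to obtain the key parameters required for the formula". The formula is n = φ²(ΣS_i²/g) / [Σ(X̄_i − X̄)²/(g−1)], with g=4 "representing a total of 4 groups in the study", two-tailed alpha 0.05 and 90% power.

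The size is fixed "after calculating the theoretical sample size for each group using the formula upon completion of the pilot studies". After that, "a 20% dropout rate will be considered to adjust the theoretical sample size", and the result is multiplied by 4. Section 2.1 gives equal allocation: "participants were allocated in a 1:1:1:1 ratio to one of four parallel groups".

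Section 2.9 gives no group means, SDs, pilot size or total N, and the pilot is its only stated source for the formula's inputs.

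**The concern.** Once g, alpha and power are set, φ is fixed, and the formula needs only the S_i and the X̄_i. The X̄_i enter through the variance between group means in the denominator, which is the effect the trial is powered for. Taking them from a pilot means that chance differences between small groups count as treatment effect. The denominator is then too large on average, and the n that typically comes out is too small.

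The 90% power is the only numerical sizing commitment in the article. If the prescribed calculation does not give it on average, the trial runs a higher risk of missing a real effect than stated, and the report would carry a power figure that its own method does not support.

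**Working it through.** **Inputs from section 2.9:** g=4, alpha 0.05, power 90%, dropout 20%, equal arms. **Assumed, because the article gives neither:** true effect as Cohen's f (0.10, 0.20, 0.25, 0.40) and pilot size m per arm (10 to 100). Further assumptions are normal data, mean pattern (−a, 0, 0, a), and dropout handled as n/(1−0.20).

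**1. Is the formula sound?** No N is stated, so there is none to reproduce; the formula itself can be checked. With 3 df, alpha 0.05 and 90% power, the noncentral chi-square gives λ=14.17, so φ²=14.17/3=4.72 and φ=2.17. The true variance between group means is σ_b² = g·f²σ²/(g−1) = 4f²σ²/3. With true values put in:

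- f=0.10: 4.724/0.01333 = 354.3, so 355 per arm (exact noncentral-F: 356)
- f=0.20: 4.724/0.05333 = 88.6, so 89 (exact: 90)
- f=0.25: 4.724/0.08333 = 56.7, so 57 (exact: 58)
- f=0.40: 4.724/0.21333 = 22.1, so 23 (exact: 24)

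The formula is fine when its inputs are true values.

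**2. What pilot means do to it.** Each pilot mean has variance σ²/m, so

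E[Σ(X̄_i − X̄)²/(g−1)] = σ_b² + σ²/m,

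and the denominator is inflated on average by 1 + 3/(4mf²). At f=0.25 and m=10 this is 1 + 3/(4×10×0.0625) = 2.2. At f=0.25 it is 1.6, 1.4, 1.24 and 1.12 for m=20, 30, 50 and 100. At m=20 it is 4.75 for f=0.10 and 1.23 for f=0.40.

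**3. Resulting n and power.** Simulated pilots (100,000 per setting) were put through the formula, and the true power of the four-group F test was computed at the resulting n. The first power figure is at the theoretical n, that is, after the planned 20% has been lost. The second assumes nobody is lost.

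| f (formula n with true values) | m per arm | Median n | Mean power, 20% lost | Mean power, none lost | Pilots giving ≥90% power, 20% lost |
|---|---|---|---|---|---|
| 0.10 (355) | 10 | 52 | 29% | 34% | 5% |
| | 30 | 125 | 51% | 58% | 16% |
| | 100 | 233 | 71% | 78% | 30% |
| 0.20 (89) | 10 | 37 | 55% | 63% | 19% |
| | 30 | 62 | 72% | 80% | 32% |
| | 100 | 79 | 83% | 89% | 40% |
| 0.25 (57) | 10 | 31 | 63% | 70% | 25% |
| | 30 | 45 | 77% | 84% | 35% |
| | 100 | 53 | 85% | 91% | 41% |
| 0.40 (23) | 10 | 17 | 74% | 82% | 33% |
| | 30 | 20 | 82% | 90% (just under) | 38% |
| | 100 | 22 | 87% | 94% | 40% |

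With nobody lost, the only other setting above 90% was f=0.40 with m=50 (92%).

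**4. Spread of n.** n is the reciprocal of a noisy quantity and is strongly right-skewed. At f=0.25 and m=20 the median is 40, but a tenth of pilots return 19 or fewer and a tenth 123 or more. The mean n is about 73, above the 57 needed.

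**5. No true effect.** The observed between-group variance is then (σ²/m)·χ²₃/3, so n ≈ 14.17·m/χ²₃. Taking the chi-square median of 2.366 and m=10 gives 14.17×10/2.366 ≈ 60 per arm; the simulated median is 59. The rule returns a feasible-looking trial even when the treatments do nothing.

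**The case against.** **The article does not say that raw pilot means are entered.** It says that the pilot supplies the key parameters. A full protocol could add shrinkage, a confidence limit or a minimum important difference. The absence of such detail from a condensed article is not itself an error. But the formula's only data inputs are the S_i and X̄_i, and section 2.9 says n is calculated from it once the pilot is done. That is a stated rule, and it is faulty as stated.

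**A reader might infer that this trial will lack 90% power, or that n always comes out too small.** Neither follows. The shortfall is in expected power and in the median n. About 5–42% of simulated pilots give an n with at least 90% power, and mean n is often at or above the requirement. Some pilots would oversize the trial, which wastes patients.

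**A reader might infer that a false negative becomes likely.** At f=0.20–0.25 with 10 to 30 per arm, mean power of 55–77% means a miss rate of 23–45%: much more than 10%, but below one half. A miss is more likely than not only at the smallest assumed effect (f=0.10) with pilots of about 20 per arm or fewer.

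**A large pilot, or less dropout than planned, shrinks the problem.** This stands. With 100 per arm, mean power is 85–87% at f=0.25–0.40, and above 90% if nobody is lost. But at f=0.25 such a pilot has 400 patients, more than the 4×58=232 completers that the main trial needs. The dropout allowance is also not spare: the Discussion itself expects that dropout may be high.

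**Nothing in section 2.9 says that pilot patients enter the main analysis,** so that is no part of this point.

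**Conclusion.** The point holds as a statement about the rule. The upward bias in the denominator is algebraic and needs no assumption beyond a finite pilot. The size of the power loss depends on the pilot size and true effect, which the article does not give, so only a range can be stated. If the planned dropout occurs, expected power is below 90% in every setting examined, from a shortfall of about 3 points (f=0.40, 100 per arm) to about 61 points (f=0.10, 10 per arm). With no dropout, 90% is reached only with pilots of 50 to 100 per arm and a medium or large effect. Confidence is high on direction and moderate on size. The formula and its φ are correct; the fault lies in using pilot means as the effect to be detected.

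**What to change.** Revise section 2.9 so that:

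- the group differences in the formula are set in advance from a justified smallest worthwhile difference;
- the primary measure that sizes the trial is named, since Table 7 lists both MBF by contrast echocardiography and SDS by perfusion imaging;
- the pilot is used only for the pooled SD and for feasibility, preferably with a conservative upper confidence limit for the SD (the exact limit is a matter of choice);
- n per arm and total N are computed from those inputs and stated.

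For scale, with 20% dropout the same formula gives 355/0.8=444, 57/0.8=72 or 23/0.8=29 per arm for an assumed f of 0.10, 0.25 or 0.40. If pilot means are kept as the effect, the 90% power statement should be withdrawn.

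The cost is rewording one section and one recalculation, which is cheap while N is still to be set. The downside is that n, or the power that can honestly be stated, may look less favourable.
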